#### Descriptive statistics

Continuous variables will be presented as mean ± standard deviation for normally distributed data or median (interquartile range) for non-normally distributed data. Categorical variables will be summarized as frequencies and percentages.

#### Comparative analyses

Between-group comparisons of continuous variables will use the independent samples t-test or Mann–Whitney U test, as appropriate. Categorical variables will be compared using the Chi-square test or Fisher’s exact test. For repeated measures (TCM syndrome score, QoL), baseline-adjusted mixed models for repeated measures (MMRM) will be used, with treatment group, visit, treatment-by-visit interaction, and baseline value as fixed effects, and participant as random effect.

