#### Follow-up and assessments

Follow-up visits will occur every 3 months, as outlined in Table 2, and will include clinical evaluation, imaging studies, laboratory testing, and assessment of adverse events. Imaging for tumor response assessment will be performed every 8 weeks from randomization until disease progression. The efficacy of YFXJD will be evaluated through progression-free survival, TCM symptom scores, activity levels, biochemical parameters, and exploratory biological indicators. Safety will be assessed according to protocol-defined criteria. The trial flowchart is presented in Figure 1.

**Table 2 tab2:** Schedule of trial.

Assessment/Time point	Screening	Baseline/Initiation	Treatment period	Treatment period	Long-term follow-up	End-of-treatment visit	Survival follow-up
	D -7	D0	D90 ± 7	D180 ± 7	D365 ± 7	Upon PD/Discontinuation	
Procedures							
Informed consent	✓						
Eligibility review	✓						
Data collection							
Demographic information	✓						
History of NSCLC & treatment	✓						
History of other diseases	✓						
Randomization & drug dispensing		✓	✓ (Re-supply)	✓ (Re-supply)			
Primary endpoints							
1. PFS (RECIST 1.1)			Imaging per protocol	Imaging per protocol	Imaging per protocol	✓ (Confirm PD)	Record death
2. TCM Syndrome Score	✓ (Baseline)		✓ (Interim)	✓ (Primary Time Point)			
Secondary endpoints (Efficacy)							
Tumor response (ORR/DCR)			✓	✓	✓	✓ (Final)	
Quality of life (EORTC QLQ)	✓ (Baseline)		✓	✓	✓		
Performance status (KPS)	✓ (Baseline)		✓	✓	✓		
Biomarkers							
Lymphocyte subsets	✓ (Baseline)		✓	✓	✓		
Inflammatory cytokines	✓ (Baseline)		✓	✓	✓		
Tumor markers	✓ (Baseline)		✓	✓	✓		
Safety assessments							
Clinical laboratory tests							
CBC, hepatic & renal function	✓	✓	✓	✓	✓	✓	
Urinalysis & stool routine	✓	✓	✓	✓	✓	✓	
AE/SAE collection	✓	✓	✓	✓	✓	✓	
EGFR-TKIs specific AE recording		✓	✓	✓	✓	✓	
Concomitant medication record		✓	✓	✓	✓		
Proportion with dose Mod./Disc.			Recorded	Recorded	Recorded	✓ (Final)	
Study administration							
Protocol deviation record		✓	✓	✓	✓		
CRF completion		✓	✓	✓	✓	✓	

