#### Secondary outcomes

Change in TCM Qi-Yin Deficiency Syndrome Score: The absolute change in the total score from baseline to 6 months (D180 ± 7), assessed using a pre-specified and validated TCM syndrome scale specific for Qi-Yin deficiency in lung cancer. The scale ranges from 0 to 48, with higher scores indicating more severe symptoms. The minimal clinically important difference (MCID) is 4 points. All TCM assessors will undergo a 2-day training session with standardized patients, and inter-rater reliability (kappa ≥ 0.80) will be established prior to study initiation.Objective Response Rate (ORR) and Disease Control Rate (DCR) as per RECIST 1.1 (15).Duration of Response (DOR).Overall Survival (OS).Change in health-related quality of life assessed using the European Organization for Research and Treatment of Cancer Quality of Life Questionnaire Core 30 (EORTC QLQ-C30) (16) and its lung cancer-specific module (QLQ-LC13) (17).Change in Karnofsky Performance Status (KPS) score (18).Incidence, type, severity, and relationship to study treatment of all Adverse Events (AEs) and Serious Adverse Events (SAEs), graded according to the National Cancer Institute Common Terminology Criteria for Adverse Events (NCI CTCAE) Version 5.0 (19).

Evaluation of EGFR-TKIs-related specific adverse reactions:Rash: A validated skin toxicity assessment tool (e.g., HFSR-14 scale or specialized assessment based on CTCAE v5.0 dermatology criteria) will be used to record the incidence, maximum severity (grade), time to onset, duration, and management measures (e.g., topical/systemic medications, dose modifications) of rash.Diarrhea: The incidence, maximum severity (graded per CTCAE v5.0 gastrointestinal criteria), duration, frequency of diarrhea will be recorded, along with the proportion of patients requiring EGFR-TKIs dose modification, interruption, or discontinuation due to diarrhea. The use of anti-diarrheal medications will also be documented.The proportion of patients requiring EGFR-TKIs dose reduction, interruption, or permanent discontinuation due to the above or any other AEs.Changes in serum levels of inflammatory cytokines (IL-2, IL-6, IL-10, TNF-*α*, IFN-*γ*).Changes in peripheral blood lymphocyte subsets (CD3^+^, CD4^+^, CD8^+^, CD4^+^/CD8^+^ ratio, NK cells).Changes in serum tumor marker levels (CEA, CYFRA21-1, SCC-Ag, NSE).

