### Randomization and blinding

To ensure balanced allocation, centralized randomization using an interactive web response system (IWRS) with variable block sizes (4 and 6) will be performed by an independent statistician. The randomization method will employ a 1:1 allocation ratio using SAS statistical software. Drug packages will be labeled with randomization codes; allocation codes will be sealed and stored separately. Participants will be enrolled sequentially by clinical staff and randomized via the IWRS. The treatment code will be retained by an independent statistician or pharmacy, not the principal investigators. All individuals involved in the trial—including clinicians, nurses, researchers, and patients—will remain unaware of the treatment assignments. Emergency unblinding will occur only when knowledge of assignment is essential for clinical management of a life-threatening condition; an SAE will not automatically trigger unblinding or withdrawal. Participants will be randomized before the first osimertinib dose. In the event of a life-threatening emergency, sealed emergency letters containing unblinding information will be available. A report of any serious AEs must be submitted to the principal investigators within 24 h. After the follow-up period ends, the treatment codes will be disclosed following the completion of data analysis.

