#### Survival analysis

PFS and OS will be estimated using the Kaplan–Meier method, and groups will be compared with the log-rank test. The Cox proportional hazards model will be used to estimate hazard ratios (HRs) and corresponding 95% confidence intervals, with potential adjustment for prespecified stratification factors. Proportional hazards assumptions will be checked using Schoenfeld residuals.

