### Additional analyses

Interim analysis for safety and futility is planned after 50% of the planned PFS events have been observed. A futility boundary will be defined using the Lan-DeMets O’Brien-Fleming spending function. The DMC will have clear decision authority regarding continuation, modification, or termination.

Subgroup analyses are prespecified based on factors such as EGFR mutation subtype (e.g., exon 19 del vs. L858R), baseline TCM syndrome score severity, and presence of brain metastases. These analyses are explicitly labeled as exploratory due to limited power for interaction testing.

Logistic regression analysis will be employed to explore factors influencing tumor response rates. A two-sided *p* < 0.05 will be considered statistically significant for the primary endpoint. No adjustment for multiple comparisons will be made for exploratory secondary endpoints, and results for these will be interpreted as hypothesis-generating.

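### KPS and the biomarkers are left to two-sample tests on change although QoL, on the same visit schedule, gets a baseline-adjusted MMRM; the optional Cox adjustment also names no factors

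*Protocol article*

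**What the plan says.** The Comparative analyses section gives a general rule: "Between-group comparisons of continuous variables will use the independent samples t-test", with the Mann–Whitney U test as the alternative. One exception follows: "For repeated measures (TCM syndrome score, QoL), baseline-adjusted mixed models for repeated measures (MMRM) will be used". That model has treatment, visit, their interaction and the baseline value as fixed effects. The parenthesis names two outcomes and carries no wording such as 'for example'.

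The Secondary outcomes section defines further continuous outcomes as changes: "Change in Karnofsky Performance Status (KPS) score", and likewise changes in five serum cytokines, in lymphocyte subsets and in four tumour markers. Table 2 marks a baseline and then D90, D180 and D365 for KPS and all three biomarker groups. The QoL row has the same ticks. The text on biomarker sample processing confirms these four blood sampling times.

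For PFS, the Survival analysis section compares the arms with a log-rank test and estimates the hazard ratio from a Cox model "with potential adjustment for prespecified stratification factors". The Randomization and blinding section describes 1:1 allocation through a web system "with variable block sizes (4 and 6) will be performed by an independent statistician". It lists no strata, and no other section names a stratification factor. The nearest thing to a list of baseline factors is the set of exploratory subgroups under Additional analyses: "EGFR mutation subtype (e.g., exon 19 del vs. L858R), baseline TCM syndrome score severity, and presence of brain metastases".

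**The concern.** Outcomes of the same type on the same schedule are analysed in two ways, and no reason is given. QoL gets a model that uses all visits and conditions on baseline. KPS and the biomarkers get a test that does neither, unless one reads them into a list that does not mention them. The baseline values are collected in any case, so the precision lost is lost for nothing. An arm that starts with higher values by chance will also tend to show a different change through regression to the mean, and a two-sample test on change does not correct for that.

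For the primary endpoint, the adjustment of the hazard ratio is optional and refers to factors the article does not identify. Read literally, this leaves open both whether to adjust and for what, on the estimate that will be quoted most.

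**Working it through.** The documents give no standard deviation or correlation for KPS or the biomarkers, so there is no plan figure to reproduce. The size below rests on assumed correlations, shown as a range.

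**1. Efficiency of baseline adjustment.** Let the outcome have the same SD, σ, at baseline and follow-up, with correlation ρ between them. At a single visit, the per-patient variance relevant to the treatment comparison is:

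- change score: 2(1 − ρ)σ²
- baseline-adjusted: (1 − ρ²)σ²
- ratio, change over adjusted: 2(1 − ρ)/(1 − ρ²) = 2/(1 + ρ)

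For illustration, power is for an assumed true difference of 0.4 SD, 100 patients per arm (Sample size section) and two-sided 0.05.

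| ρ (assumed) | Change, in σ² | Adjusted, in σ² | Ratio | Power, change | Power, adjusted |
|---|---|---|---|---|---|
| 0.3 | 1.40 | 0.91 | 1.54 | 0.67 | 0.84 |
| 0.5 | 1.00 | 0.75 | 1.33 | 0.81 | 0.90 |
| 0.7 | 0.60 | 0.51 | 1.18 | 0.96 | 0.98 |

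With the stated 20% dropout (80 per arm) and ρ = 0.5, power is 0.72 on change and 0.83 adjusted.

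**2. Exposure to chance imbalance.** With 100 per arm, the baseline difference between arms has a standard error of √(2/100) = 0.141 SD. If the arms differ by δ at baseline, the change-score difference is shifted on average by −(1 − ρ)δ. For an imbalance of one standard error, the size of that shift is 0.7 × 0.141 = 0.10 SD at ρ = 0.3, 0.5 × 0.141 = 0.07 SD at ρ = 0.5, and 0.3 × 0.141 = 0.04 SD at ρ = 0.7. Over repeated randomizations these shifts average to zero.

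**3. The Cox model.** The Survival analysis section presupposes stratification factors, while the Randomization and blinding section gives only the system, the ratio and the block sizes. If strata exist, the description of randomization is incomplete. If they do not, the Survival analysis wording refers to nothing.

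The size was gauged by simulating 3,000 trials with 100 per arm and a treatment HR of 0.66. The assumed prognostic HRs were 1.5 for L858R (prevalence 40%) and 1.6 for brain metastases (prevalence 30%). The data cut was month 24, which matches enrolment from January 2026 and final primary follow-up by December 2027 (Trial status). Power was 44.2% unadjusted and 46.2% adjusted. A repeat run gave 45% and 47%. The Monte Carlo error of one such figure is √(0.44 × 0.56/3000), or about 0.9 points.

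The choice between the two estimates matters more than the power gain. Under the same assumptions, about 29% of trials had an imbalance of 10 percentage points or more in at least one of the two factors. In about 10% of trials the adjusted and unadjusted hazard ratios differed by a factor of about 1.10 or more.

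**The case against.** A reader might infer that the two-sample tests ignore baseline and are biased. The documents do not support this. The outcomes are defined as changes, so baseline enters by subtraction, and the comparison is unbiased under randomization. For the same reason, a comparison with a test on the follow-up value alone would be beside the point, because the article does not define these outcomes that way.

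The assignment of KPS and the biomarkers to two-sample tests is by elimination. The MMRM sentence opens with repeated measures in general, and the parenthesis could have been meant as illustrative. That reading is possible, but nothing in the wording signals it, and no other method is given for these outcomes. They also carry little weight: the article calls the biomarker analyses exploratory and treats exploratory secondary endpoints as hypothesis-generating. KPS moves in steps of 10, so a rank test is defensible and a normal-theory model is not plainly better for it. This stands, and it is why the rank test should be kept.

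On PFS, a reader might infer that randomization is unstratified and the adjustment set empty, or that the primary test is compromised. The first is an inference from silence in a condensed article; what can be said is that no factor is named. The second does not follow: the log-rank test is valid without adjustment, the unadjusted hazard ratio is a legitimate marginal estimate, and the wording speaks only of potential adjustment. Not listing covariates would in itself be missing detail that another document may supply. What remains is that two sections of the article do not fit together and the adjustment is left optional.

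**Conclusion.** The point holds as an inexpensive improvement, not as an error that invalidates an analysis. For KPS and the three biomarker groups, two-sample tests on change carry 54% more variance than a baseline-adjusted analysis at ρ = 0.3, 33% more at 0.5 and 18% more at 0.7. These figures assume equal variances at baseline and follow-up and a single-visit comparison; the correlations are assumptions too. The tests are valid but less precise, and exposed to whatever baseline imbalance occurs. Only secondary and exploratory endpoints are affected.

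The Cox wording is a minor second point. The gain in PFS power is about 2 points at month 24 under assumed prognostic effects, and no passage establishes that EGFR subtype or brain metastases are strong prognostic factors in this population. The reason to act is that the plan should settle in advance whether, and for what, the hazard ratio is adjusted.

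**What to change.** In Comparative analyses, extend the baseline-adjusted MMRM to KPS, cytokines, lymphocyte subsets and tumour markers, on the log scale where a marker is skewed. Keep the Mann–Whitney test on change as a sensitivity analysis, notably for KPS.

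Reconcile Survival analysis with Randomization and blinding. If strata were used, name them in both places and adjust for them. If not, replace the reference to stratification factors with a fixed covariate set that is not optional and is already needed for the subgroup analyses, for example EGFR subtype and baseline brain metastases. Report that adjusted hazard ratio beside the log-rank test and the unadjusted hazard ratio.

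The cost is analysis wording, a little programming, and the ethics committee approval that the article requires for any amendment. No new data are needed. With 38 patients enrolled by July 2026 and treatment codes still closed, the change can be made before any unblinded result is seen.

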### Sample size

The sample size for this study was calculated based on the primary outcome of progression-free survival (PFS). Based on the FLAURA trial, the median PFS for osimertinib monotherapy is approximately 18.9 months. To achieve 80% power at a two-sided significance level of α = 0.05 for detecting a clinically meaningful difference, a target hazard ratio (HR) of 0.66 was assumed, corresponding to a median PFS of approximately 28.6 months in the experimental group (an absolute extension of 9.7 months). This effect size is consistent with the HR observed in the CATLA trial (HR 0.68).

Using the Schoenfeld formula for the log-rank test, the required number of PFS events (d) is calculated as:
$$d=4\times {\left(Z\_(1-\alpha /2)+Z\_(1-\beta )\right)}^{2}/{\left(\ln\;\mathrm{HR}\right)}^{2}$$

With α = 0.05 (two-sided), β = 0.20 (power = 0.80), Z_(1-α/2) = 1.96, Z_(1-β) = 0.84, and HR = 0.66:
$$d=4\times {\left(1.96+0.84\right)}^{2}/{\left(\ln\;0.66\right)}^{2}\approx 176\;\text{events}$$

Under a 1:1 randomization ratio with an accrual period of 12 months, a minimum follow-up of 12 months, and an expected event rate of approximately 65% at the end of follow-up, the required total sample size is approximately 270 patients (135 per group). Accounting for an estimated dropout rate of approximately 20%, we plan to enroll 200 patients (100 per group) to ensure that sufficient patients complete the primary endpoint assessment. The planned enrollment of 200 patients is expected to yield approximately 130 PFS events, providing approximately 75% power at the planned analysis. An interim analysis for futility is planned after 50% of the expected PFS events have been observed, with the option to increase sample size if warranted by conditional power calculations.

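### Maximum rash and diarrhea grade is ordinal, but the only test the protocol names for categorical variables ignores the order of the grades (minor)

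*Protocol article*

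**What the plan says.** Under Secondary outcomes, the protocol article sets out what is recorded for rash: "incidence, maximum severity (grade), time to onset, duration, and management measures". For diarrhea it lists incidence and then "maximum severity (graded per CTCAE v5.0 gastrointestinal criteria), duration, frequency of diarrhea will be recorded". In both cases severity stands next to incidence as a separate item, so it is more than a yes/no event.

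Under Comparative analyses there are two general rules for single-time comparisons. The first is "Between-group comparisons of continuous variables will use the independent samples t-test or Mann–Whitney U test, as appropriate". The second is "Categorical variables will be compared using the Chi-square test" or Fisher's exact test. Mixed models are reserved for the TCM syndrome score and quality of life. No section names a method for ordered categories or says which rule applies to toxicity grades.

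Additional analyses leaves exploratory secondary endpoints unadjusted and treats them as hypothesis-generating.

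**The concern.** A CTCAE grade, with no event as zero, is an ordered category. Under the two rules it is not continuous, so it falls to Chi-square or Fisher's exact. On a table of two arms by k grades, both are tests of general association: the p-value stays the same if the grade columns are permuted. The Chi-square test spreads its power over k − 1 degrees of freedom. If the question is whether severity shifts down or up as a whole, a one-degree-of-freedom ordered test usually answers it better from the same data.

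Direction matters in this trial. The Introduction cites a trend toward reduced toxicity as part of the rationale. Objectives includes the incidence and characteristics of treatment-related adverse events. The herb-drug interaction section provides for monitoring of overlapping gastrointestinal toxicity. What is at stake is efficiency on secondary safety outcomes, not the validity of the trial's main result.

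**Working it through.** **No figure to reproduce.** The protocol gives no power, grade distribution or effect size for rash or diarrhea severity, so the check is a scenario calculation.

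**Inputs from the protocol.** Sample size: "we plan to enroll 200 patients (100 per group"). Dropout is put at about 20%, which leaves about 100 × 0.8 = 80 per arm as a lower case. The two-sided 0.05 level is stated for the primary endpoint and is assumed here for the grade comparison.

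**Assumed inputs.** Control-arm grade distributions with three to five levels, and a proportional-odds shift with odds ratio OR. For each cut-point g, odds(grade ≥ g, YFXJD) = OR × odds(grade ≥ g, control).

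Example with control 42/38/15/5% for grades 0/1/2/3 and OR 0.5:
- grade ≥ 1: 0.58/0.42 = 1.381; × 0.5 = 0.690; probability 0.690/1.690 = 0.408
- grade ≥ 2: 0.20/0.80 = 0.250; × 0.5 = 0.125; probability 0.111
- grade ≥ 3: 0.05/0.95 = 0.0526; × 0.5 = 0.0263; probability 0.026

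The YFXJD arm is then 59.2/29.7/8.5/2.6%.

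**Method.** 20,000 simulated trials per scenario (simulation standard error at most √(0.25/20,000) = 0.35 points), comparing the Pearson Chi-square test on the full grade table with the tie-corrected Wilcoxon rank-sum test.

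**Power with 100 per arm, Chi-square → Wilcoxon (gain in points):**

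| Control distribution, % | OR 0.6 | OR 0.5 | OR 0.4 |
|---|---|---|---|
| 42/38/15/5 | 33 → 48 (16) | 56 → 73 (17) | 81 → 92 (11) |
| 30/40/20/10 | 34 → 50 (16) | 59 → 75 (17) | 84 → 94 (10) |
| 60/25/10/5 | 28 → 41 (14) | 46 → 64 (18) | 70 → 85 (15) |
| 40/30/18/10/2 | 29 → 49 (20) | 52 → 74 (22) | 78 → 93 (14) |
| 45/35/15/4/1 | 28 → 47 (19) | 50 → 72 (22) | 77 → 91 (15) |
| 45/40/15 (three levels) | 37 → 47 (10) | 60 → 71 (11) | 84 → 91 (7) |

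Gains are taken from unrounded powers. With four or five levels and odds ratios of 0.6 to 0.4, the gain is about 9 to 22 points over the distributions tried. At an odds ratio of 0.3 both tests are near their ceiling and the gain is about 1 to 7 points, for example 96% → 99%. At 0.7 it is about 6 to 13 points. Taking three levels and the 0.3 cases together gives about 1 to 11, apart from cases as small as 0.7.

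**Lower case, 80 per arm, OR 0.5.** 40/30/18/10/2: 42% → 64%. 60/25/10/5: 37% → 55%. 45/40/15: 50% → 62%. The picture is the same.

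**Type I error.** At OR 1 both tests reject in about 4 to 5% of trials, so the gain is not bought with false positives.

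**Where the shift is not uniform.** Two patterns keep incidence unchanged and move patients only out of the highest grades. Both are stochastically ordered, with no crossing. Power with 100 per arm:

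| Control → YFXJD, grades 0/1/2/3, % | Chi-square | Wilcoxon | Fisher's exact, grade ≥ 3 |
|---|---|---|---|
| 42/33/15/10 → 42/38/18/2 | 52% | 9% | 59% |
| 40/30/18/12 → 40/40/17/3 | 60% | 17% | 61% |

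The last column sums Binomial(100, p₁) × Binomial(100, p₂) probabilities over all outcomes where Fisher's two-sided p is below 0.05, with p₁, p₂ = 10%, 2% and 12%, 3%. In these patterns the rank test is much the weaker test, and a grade 3 or higher comparison recovers what it misses.

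**The case against.** The strongest reply is that the protocol never says grades will be tested as unordered categories. Secondary outcomes says they are recorded, Comparative analyses has one general sentence, and assigning a test to each safety variable is often left to a statistical analysis plan, which is not shown. Grades might also be dichotomised, where Chi-square or Fisher's exact is suitable. This stands in part: the application to grades is an inference, and an analysis plan could refine it. The point survives because the protocol does state a rule for categorical variables, and reserves the rank test for continuous ones. A plan that follows that wording would carry the mismatch forward.

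A reader might infer that the stated test is in general the least able to show a change in severity, or that the only price of a rank test is insensitivity to non-monotone differences. Neither is supported. A reduction limited to severe grades is monotone, is a plausible form of reduced toxicity, and is detected far better by Chi-square.

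A reader might also infer a fixed loss of 10 to 22 points. The documents supply no grade distribution, odds ratio or proportional-odds assumption, so no unconditional figure can be given.

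Nor do the documents support reading this as a safety signal likely to be missed. Incidence, the proportions with dose modification, overlapping-toxicity monitoring and data monitoring committee review do not depend on this p-value. Sparse high-grade cells are no separate fault, since Fisher's exact test is already named.

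**Conclusion.** The concern holds in a limited form. Maximum rash and diarrhea grade is ordinal, and the only test the protocol names for categorical variables discards the order. For a general shift in severity, a rank test is the better choice: about 9 to 22 points more power with four or five levels and odds ratios of 0.6 to 0.4, and about 1 to 11 with three levels or at an odds ratio of 0.3. These figures rest on 100 per arm, a two-sided 0.05 level, assumed control distributions and proportional odds. The ranking reverses when only the highest grades fall.

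The stated test is valid, and type I error is unaffected. These are secondary outcomes with no power target, and the primary progression-free survival analysis is untouched. Severity: minor.

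**What to change.** Under Comparative analyses, add wording to this effect: maximum CTCAE grade of rash and of diarrhea (no event = 0) will be compared between arms with the tie-corrected Wilcoxon rank-sum test, with a proportional-odds common odds ratio and 95% confidence interval; the table of grades by arm will be shown, and grade 3 or higher will be compared by Fisher's exact test. Keep Chi-square or Fisher's exact for binary and nominal outcomes, such as incidence, response rates and the proportions with dose modification.

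Name the Wilcoxon test as the main severity comparison and the grade 3 or higher test as supporting, so that the more favorable of the two is not picked afterwards.

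The cost is a sentence or two of wording and no new data. The downside is that the rank test is less sensitive to differences that are not a general shift, including a reduction in severe grades alone, which the retained comparison is there to cover. Trial status reports 38 of 200 patients enrolled in July 2026 and database lock in the first quarter of 2028, so the change can be made while the trial is blinded.
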